#### Periods of implementation (approximately 3 months)

Between the workshops the worksites will test and implement their initiatives, e.g. using the Model of Improvement from the ITASPA Package of Change. At each worksite, the ITASPA Facilitators participate in two of the ITASPA Committee’s meetings every implementation period to support the worksites and ensure an integrated approach.

### Data collection and study materials

#### Screening questionnaire

The screening questionnaire contains questions about job title, sex, age, country of birth, years lived in Denmark, job seniority, education, smoking, alcohol consumption, level of MSDs, safety culture at the worksite, psychosocial wellbeing, and diagnosis with one or more of the following diseases: asthma, allergy, diabetes, cardiovascular or skin diseases, and mental disorders.

#### Data collection at baseline and after the periods of implementation

The data collection will be conducted at baseline, before the first learning workshop, and after each period of implementation, approximately every third month throughout the year of scientific evaluation, summing up to five data collections in total (Fig. 4). The data collection will be conducted by the ITASPA facilitators at a health check encompassing a questionnaire-based interview and objective measurements.

**Fig. 4 Fig4:**
[figure not shown]
SPIRIT Flow diagram of the ITASPA intervention

The questionnaire-based interview includes questions about the level of physical activity in occupational and leisure time, eczema, and self-reported health. Functionality will be measured by the ICF-based Work Rehabilitation Questionnaire (WORQ) (https://myworq.org/). The Short Form of the Örebro Musculoskeletal Pain Screening Questionnaire will be used to measure MSDs [18]. Psychosocial wellbeing will be measured via the Health Survey SF-12 [19]. Finally, safety culture will be measured by the Nordic Occupational Safety Climate Questionnaire (NOSACQ-50) [20].

The objective measurements include body weight (kg), height (m), percent body fat, resting heart rate (beats per minute), and blood pressure (mmHg). Bodyweight, percent body fat, and height will be measured while the participant is wearing light clothes and no shoes. The estimated weight of clothes (1.5 kg) will be subtracted from body weight. Percent body fat will be estimated by bioelectric-impedance-analysis. Both body weight and percent body fat will be measured by a Segmental Body Composition Monitor, Innerscan V, BC545N (TANITA, produced in Japan). If participants have a pacemaker or are pregnant, the analysis of percent body fat will not be made. Body height will be measured on a mobile stadiometer Seca 213 (Seca, produced in China). Body mass index (BMI) will be estimated by the equation of BMI = (body weight (kg)/body height (m)^2^). Resting heart rate and blood pressure will be measured three times on the left arm after 15 min of sitting at rest using an Omron Model M3, automatic upper arm BP monitor (Omron healthcare, produced in Vietnam).

At baseline, and after the periods of implementation, we will collect data on sickness absence, staff turnover, and productivity combined with interviews with the chairperson of the ITASPA committee. These data will be collected for a financial evaluation of the overall ITASPA intervention at each worksite.

### Process and implementation evaluation

The implementation of the initiatives will be tracked by the research group using quantitative and qualitative methods, allowing for triangulation of data across methodologies [21].

The quantitative process tracking will be based on the data collected by the ITASPA committees during the implementation periods. Data will be used to monitor the fidelity and dose (the amount of intervention delivered) of the planned initiatives, following the principles of process evaluation [21].

The qualitative process tracking will be based on focus group interviews consisting of members of the ITASPA committee at each worksite after the second learning workshop and an individual semi-structured interview with the chairperson of the ITASPA committee midway through each implementation period. Data on implementation experiences will be collected and feedback on the effect of the chosen outcome, for the particular period of implementation, will be given. This has two purposes: 1) to collect data on factors facilitating and hindering the implementation of the initiatives, and 2) to give feedback to the worksites regarding the effect of the chosen outcome, based on the initiative in the ongoing period of implementation. The focus groups are directed by a semi-structured interview guide including questions about the specific interventions and reflections on intervention delivery, such as observations on contextual factors, barriers, and facilitating factors of intervention implementation [21]. Thus, the interviews will be tailored to the context and initiative at each worksite and provide input for the next period of implementation. Conversation objectives, topics, and materials discussed will be documented.

### Effect evaluation

Data from the health checks will be used to evaluate the effect of the initiatives after each implementation period. Preliminary descriptive analysis will be conducted and discussed with the ITASPA committee after each implementation period to ensure that only beneficial and effective initiatives are continued in the next implementation period and to guide the development of future initiatives.

### Statistical analysis

Descriptive analyses of baseline data and health check data will be conducted after the implementation periods. Frequencies and distribution of participants across variables will be reported (amount and percentages). Differences between baseline data and the follow-ups within and between participating worksites will be reported by the use of chi^2^ test for categorical variables and paired and independent sampled t-test for continuous variables. Furthermore, differences in baseline data between those who want to participate and those who do not want to participate will be analyzed. Where appropriate, results are presented as the mean and standard deviation (Mean ± SD) or visualized in graphs and histograms.

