## Methods

### Study design

ITASPA is a worksite intervention, conducted in a stepped wedge design (Fig. 1) [16]. The stepped wedge design are assumed to increase the willingness to participate as it allows all workers to receive the intervention. The workers function as their own control and thereby, the stepped wedge design allows for an effect-evaluation, mimicking an RCT design.

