### Power calculation

The sample size estimations were based on effect expectations in MSDs, on a scale ranging from 0–10, an expected variance of 2.1, an Alpha value of 0.05, and a power of 80%. The estimation showed a cluster size of 65 participants to identify a statistically significant effect, at a 5% level, of the worksite intervention.

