### Effect evaluation and analyses

The effect evaluation will be based on a mixed-methods approach, where questionnaire data on MSDs, psychosocial wellbeing, safety culture, and workability will be measured based on the questionnaire-based interviews. The quantitative data will be analyzed based on the intention-to-treat principle in linear mixed models with random slope and intercept. The repetitive measurements within and between participants will be accounted for by nesting participants in clusters at the worksite level. The intervention will be included as a categorical variable with two levels, comparing the intervention period with the control period as a fixed effect in the model. Intercorrelation of repeated measurements will be included in the models as a random effect. Participants missing data on exposure or outcome variables will be excluded from analyses. All analyses will be conducted in SAS version 9.4 and/or SPSS version 27.0.

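### Within-worksite change in categorical variables is assigned a chi-square test although the same workers are measured repeatedly, so these descriptive p-values come out too large

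*Protocol article*

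**What the plan says.** The Statistical analysis section of the protocol article describes what is compared as "Differences between baseline data and the follow-ups within and between participating worksites", and says that these differences "will be reported by the use of chi^2^ test for categorical variables and paired and independent sampled t-test for continuous variables". Continuous variables therefore get both a paired and an independent-samples test, while categorical variables get one test with no paired form.

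Other sections show that the comparison over time is within person. Study design says "The workers function as their own control". The data collection section schedules a baseline, a measurement before the first learning workshop and one after each implementation period, "summing up to five data collections in total".

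The effect analysis is separate. Under Effect evaluation and analyses, the quantitative data are "analyzed based on the intention-to-treat principle in linear mixed models with random slope and intercept", and "Intercorrelation of repeated measurements will be included in the models as a random effect". The earlier Effect evaluation section says that a preliminary descriptive analysis is discussed with each worksite's committee after every implementation period, "to ensure that only beneficial and effective initiatives are continued in the next implementation period".

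**The concern.** Pearson's chi-square test on a table of time point by answer category treats every answer as coming from a different person. Here each worker contributes an answer at both time points. If a worker's two answers are positively correlated, as is usual, the difference between the two proportions varies less than the test assumes. The statistic is then too small and the p-value too large.

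What is at stake is missed change. A real shift in a categorical item within a worksite may be reported as non-significant when a paired test on the same data would detect it. The article attaches some use to descriptive results between implementation periods, so an insensitive test could make a useful initiative look ineffective.

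**Working it through.** **The plan's own figures.** The article reports no calculation for this test. Its only computed figure is the cluster size of 65, from "an expected variance of 2.1, an Alpha value of 0.05, and a power of 80"%. The effect size is not stated, so 65 cannot be reproduced, and the point does not depend on it. It serves below only as an illustrative number of workers.

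**Inputs.**
- From the document: paired structure (Study design; data collection section) and chi-square for categorical variables (Statistical analysis). The two-sided 5% level used below is conventional.
- Assumed, not in the document: the within-person correlation rho of a binary item, and its prevalence.

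**Step 1: the variance.** Take n workers and a binary item with the same prevalence p at both times (equal margins).
- True variance of the difference in proportions: 2p(1-p)(1-rho)/n.
- Variance used by chi-square: 2p(1-p)/n.
- The chi-square statistic is therefore (1-rho) times the correct paired statistic. It rejects only when the correct |Z| exceeds 1.96/sqrt(1-rho).

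**Step 2: true type I error and power.**
- True type I error = 2 × [1 - Phi(1.96/sqrt(1-rho))].
- Where the paired test has 80% power, its Z has mean 1.96 + 0.84 = 2.80. Power of chi-square = Phi(2.80 - 1.96/sqrt(1-rho)).

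| rho (assumed) | 1.96/sqrt(1-rho) | True type I error | Power of chi-square when the paired test has 80% |
|---|---|---|---|
| 0 | 1.96 | 5% | 80% |
| 0.4 | 2.53 | 1.1% | Phi(0.27) = 61% |
| 0.6 | 3.10 | 0.2% | Phi(-0.30) = 38% |
| 0.8 | 4.38 | 0.001% | Phi(-1.58) = 6% |

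**Step 3: simulation check.** Paired binary data, 100,000 replicates per setting, baseline prevalence 0.5.
- With n = 65 and no change, chi-square rejected in 1.7%, 0.5% and 0.05% of replicates at rho 0.3, 0.5 and 0.7. McNemar's test rejected in 5.3%, 4.9% and 4.4%.
- With n = 65 and a fall from 50% to 35%, power for chi-square against McNemar was 39% against 55% (rho 0.3), 37% against 69% (rho 0.5) and 33% against 93% (rho 0.7).
- With n = 200 and the same fall, the gap was small because both tests had high power: 90% against 95% at rho 0.3, and 94% against 99% at rho 0.5.

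**Step 4: one worked table.** Of 65 workers, 12 are positive at both times, 14 change to negative, 4 change to positive and 35 are negative at both. So 26 are positive at baseline and 16 at follow-up.
- Correlation: (12×35 - 14×4)/sqrt(26×39×16×49) = 364/891.6 = 0.41.
- Chi-square: pooled proportion 42/130 = 0.323, statistic 3.52, p = 0.061.
- McNemar: (14 - 4)²/(14 + 4) = 5.56, p = 0.018 (exact p = 0.031).

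The same data fall on different sides of 5% depending only on whether the pairing is used.

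**The case against.** Several arguments limit the point, and most of them stand.

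- **Few variables are exposed.** The outcomes in the hypothesis are measured mainly by questionnaire instruments and analysed in linear models, and the objective measures are continuous. Most plainly categorical items (sex, education, smoking, diagnoses) sit in the screening questionnaire, which is not said to be repeated. The repeated items that might be categorical are eczema, self-reported health and physical activity, and their response formats are not given. This stands.
- **Chi-square is legitimate for part of the sentence.** Between worksites at one time point, or between participants and non-participants, different people are compared and pairing does not arise. This stands; only the within-worksite comparison over time is affected.
- **McNemar's test is itself a chi-square test, and a condensed article may have meant it.** This is possible, but the text does not say so. The same sentence names pairing explicitly for the t-test, which suggests that the authors state it where they intend it.

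A reader might also infer that these before-after tests are left open to be read as effect estimates, or that many uncontrolled p-values will yield false claims of benefit. The document does not support that. It calls these analyses descriptive, and it gives the effect evaluation its own heading and a mixed model that allows for repeated measurements. Handling of multiplicity is commonly left to an analysis plan, which is not shown here. The pairing error itself works towards missed change, not towards false positives.

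Nor does the article say that a significance test, categorical or otherwise, decides whether an initiative continues. It says that descriptive results are discussed with the committee and guide that choice.

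**Conclusion.** The point holds and is minor. As written, the plan applies an independent-samples test to paired categorical data, and the resulting p-values are too large whenever a worker's answers are positively correlated. The figures in the table rest on assumed correlations of 0.4 to 0.8, a binary item and equal margins. At a correlation near zero the distortion disappears, and with a large sample or a large change the loss of power is small in practice.

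The consequence is confined to repeated categorical items in the descriptive analysis. The effect estimates from the linear mixed models are untouched. What keeps the point from being purely cosmetic is that descriptive results from the health checks help guide which initiatives are carried forward.

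**What to change.** In the Statistical analysis section, separate the two kinds of categorical comparison:

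- For change within workers between baseline and a follow-up, use McNemar's test, with Bowker's test or a test of marginal homogeneity for more than two categories. Alternatively, use a mixed logistic model with participant and worksite effects.
- Keep the chi-square test for comparisons between different workers: between worksites at one time point, and participants against non-participants.

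This is one line of text. It needs no new data, and standard procedures exist in SAS and SPSS, the packages the article already names.

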### Effect evaluation and analyses

The effect evaluation will be based on a mixed-methods approach, where questionnaire data on MSDs, psychosocial wellbeing, safety culture, and workability will be measured based on the questionnaire-based interviews. The quantitative data will be analyzed based on the intention-to-treat principle in linear mixed models with random slope and intercept. The repetitive measurements within and between participants will be accounted for by nesting participants in clusters at the worksite level. The intervention will be included as a categorical variable with two levels, comparing the intervention period with the control period as a fixed effect in the model. Intercorrelation of repeated measurements will be included in the models as a random effect. Participants missing data on exposure or outcome variables will be excluded from analyses. All analyses will be conducted in SAS version 9.4 and/or SPSS version 27.0.

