**Fig. 1 Fig1:**
[figure not shown]
The stepped wedge design. All worksites are included at baseline. The black boxes illustrate periods where worksites will function as controls. The white boxes illustrate where worksites will function as intervention worksites and the grey boxes illustrate where the intervention is implemented and maintained

The study was approved by the Danish data protection agency (journal number REG-034–2021) and the Ethics Committee for the regional capital in Denmark (journal number SJ-927) and will be conducted in accordance with the Helsinki declaration. The first version of the Clinicaltrials.gov registration for ITASPA is registered on May 19, 2023 (NCT05866978).

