**Fig. 3 Fig3:**
[figure not shown]
Process of the ITASPA intervention

The experiences from each cycle will systematically be transferred to the next. Thus, continuous improvements and/or adjustments will be conducted.

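### A single on/off intervention term assumes an immediate, constant effect, although the programme is revised every three months; an exposure-time model should stand beside it

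*Protocol article*

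**What the plan says.** Under Effect evaluation and analyses, the Protocol article plans "linear mixed models with random slope and intercept", with participants nested in worksites. The intervention is one fixed effect, "a categorical variable with two levels, comparing the intervention period with the control period". Neither a calendar-period term nor a time-since-start term is named.

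Other sections describe what that single term must summarise:

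- **Education of the ITASPA committee:** the worksites run successive plan-do-study-act cycles, each drawing on the last, so that "continuous improvements and/or adjustments will be conducted".
- **ITASPA committee network:** the exchange between worksites begins only after the first implementation period.
- **Effect evaluation:** health-check data are to show the effect after every implementation period, and results are discussed with the committee so that "only beneficial and effective initiatives are continued in the next implementation period".
- **Data collection at baseline and after the periods of implementation:** measurements take place "approximately every third month throughout the year of scientific evaluation, summing up to five data collections in total".

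The comparisons over time under Effect evaluation and Statistical analysis are descriptive summaries, chi-square tests and t-tests. None is a time-adjusted effect by length of exposure.

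**The concern.** A two-level term is a good summary if the effect arrives at once and stays. For a programme that is adjusted, pruned and extended every three months, the effect may well differ between the first and the last exposed round. The plan itself asks for the effect after each period, which the two-level term cannot give.

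When the effect does vary, the fitted coefficient is a weighted sum of the exposure-specific effects, and the weights are set by the design and the correlations, not by the question. With period effects in the model, some weights can be negative, so that late benefit counts against the intervention. A programme that builds up slowly could then look weak, and one that fades could look better than it is.

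**Working it through.** **Plan's own figure.** The plan gives none on this point. The cluster size of 65 (Power calculation) cannot be reproduced because the expected effect is not stated as a number. It serves below only as the number of participants per worksite.

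**Inputs from the article.** Five measurement rounds, 65 participants per worksite, variance 2.1, one binary intervention term.

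**Assumptions, not in the article.** Two to four start groups; ICC 0.01 to 0.10; cluster autocorrelation (CAC) 0.8 or 1; individual autocorrelation (IAC) 0.5, or total within-person correlation 0.6; closed cohort. The weights do not depend on the variance itself, only on these correlations and on the 65.

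**Method.** Let θₖ be the true effect after k exposed periods. The covariance of a worksite's five means is

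V = 2.1·[ICC·CAC·J + ICC·(1−CAC)·I + ((1−ICC)/65)·(IAC·J + (1−IAC)·I)],

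where J is the all-ones matrix and I the identity. The generalised-least-squares coefficient of the on/off term has expectation Σ wₖθₖ. Here wₖ is the intervention element of (ΣX′V⁻¹X)⁻¹ΣX′V⁻¹dₖ, X holds the on/off column plus either an intercept or five period indicators, and dₖ marks the cells at exposure k. The weights sum to 1.

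**Worked layout.** Four start groups, first exposed at rounds 2, 3, 4 and 5; ICC 0.01, CAC 1, within-person correlation 0.6.

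| Model | w₁ | w₂ | w₃ | w₄ |
|---|---|---|---|---|
| On/off, no period term (as written) | 0.49 | 0.30 | 0.15 | 0.05 |
| On/off plus period effects | 0.962 | 0.300 | −0.081 | −0.181 |

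With period effects:

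- Constant effect 1: the weights sum to 1, so the estimate is 1. No bias.
- Linear growth (0.25, 0.50, 0.75, 1): 0.2405 + 0.150 − 0.0608 − 0.181 = 0.15. True average: 2.5/4 = 0.625.
- Absent in the first period, full afterwards (0, 1, 1, 1): 0.300 − 0.081 − 0.181 = 0.04. True average 0.75.
- Waning (1, 0.75, 0.50, 0.25): 0.962 + 0.225 − 0.0405 − 0.0453 = 1.10. True average 0.625, so overstated.

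As written, without period effects:

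- Linear growth: 0.44 against 0.625, about 71% kept.
- One-period delay: 0.51 against 0.75.
- Calendar drift: with first exposure after s rounds, the mean intervention round is (s+6)/2 and the mean control round (s+1)/2. They differ by 2.5 whatever s is. A drift of 0.1 per visit with no true effect therefore gives a false within-worksite effect of 2.5 × 0.1 = 0.25. The full calculation gives 0.25 as well.

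**Range over five-round layouts with two to four start groups.**

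| Quantity | Result |
|---|---|
| Linear growth to 1, no period term | about 70% to 88% of the average kept |
| Linear growth to 1, with period effects, four starts | 0.13 to 0.17 against 0.625 |
| Linear growth to 1, with period effects, all layouts | about 0.05 to 0.32 against 0.63 to 0.67 |
| Fast saturation (remaining gap halves each period), with period effects | 0.45 to 0.60 against 0.81 to 0.82, about 55% to 74% kept |

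**Random slope.** The article does not say on what the slope is random. With fixed variance components, neither reading repairs the linear-growth case: a random treatment slope gives 0.11 to 0.25 and a random time slope 0.13 to 0.17, against averages of 0.63 to 0.67.

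**Precision of the alternative.** In the worked layout with one worksite per start group, the SE is 0.091 for the on/off effect and about 0.14 for the exposure-time average, a ratio of about 1.5. Over the layouts the ratio is about 1.4 to 2.5.

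**The case against.** The strongest reply is that the severe shrinkage does not come from the model as printed. The article names no period term, and without one all weights are positive. A reader might infer that the written analysis would put a growing effect near zero. The documents do not support that: 0.15 and 0.04 arise only after period effects are added. What stands is that the written model still understates linear growth and is open to calendar drift, and that curing the drift brings in the negative weights.

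Second, a reader might infer that the programme is meant to build up over twelve months. No section says so. The hypothesis gives no time course, initiatives may be dropped or replaced, and the Fig. 1 legend says that "the grey boxes illustrate where the intervention is implemented and maintained", which fits a plateau equally well. Growth is plausible but not stated, and the bias depends entirely on shape.

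Third, a reader might see a contradiction between three kinds of box in Fig. 1 and two levels in the model. The legend does not show one: white and grey boxes can both count as intervention against black control boxes. The figure itself is not available here.

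Fourth, an averaged on/off effect is a common primary analysis in a stepped wedge, and extra models may sit in an SAP. This is fair, and is why the two-level model should be kept. But the two-level coding is a choice that the article fixes, and it does not answer the article's own question about the effect after each period.

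**Conclusion.** The point holds in conditional form. The two-level term is unbiased for an effect that is immediate and constant. If the effect grows with exposure, the model as written understates it moderately and is confounded with calendar time. With period effects added, linear growth could be mostly hidden and a waning effect overstated, while fast-saturating growth loses about a quarter to under half.

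The sizes rest on assumed numbers of start groups, ICCs, autocorrelations and effect shapes, so they show what the coding can do, not what it will do in this trial. The consequence is serious enough, and the remedy cheap enough, that the change should be made before the outcome data are analysed.

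**What to change.** Keep the two-level model with categorical calendar-period effects. Beside it, pre-specify an exposure-time model on the same data: the number of completed implementation periods as categorical fixed effects, plus calendar period. Report the effect at each exposure time and their average.

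Use as many exposure levels as the schedule yields. If baseline and the measurement before the first learning workshop are one round, five rounds allow up to four completed periods; if they are separate, at most three. The text can be read either way, so the schedule should say which. One sentence on how the white and grey boxes of Fig. 1 are coded would remove any doubt.

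The cost is one more model, no new data, and a wider interval for the averaged effect: an SE about 1.4 to 2.5 times that of the on/off effect, depending on the number and spacing of start groups. The longest exposure may be seen in only one start group, as in the four-start layout above, so its own estimate will be imprecise. If the average is to carry the main conclusion, the sample size needs reworking with a stated effect, ICC and number of worksites.

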### Strengths and limitations

Even though RCTs are the golden standard for intervention studies, it is not always practically possible, nor feasible, to have a control group of employees working at worksites that will not be affected by the intervention. However, the stepped wedged design will function as an RCT as it allows for comparison of control and intervention effects within the same environment, without increasing the risk of contamination between the intervention and control group, which reduces the risk of bias. Moreover, a stepped wedge design can prevent ethical objections arising from withholding an intervention anticipated to be beneficial [28]. In addition, a stepped wedge design will overcome issues with impaired organizational commitment and disappointed participants in the control group since all participants will be offered the intervention, and thus increases the participants’ obligations to the project [25]. Yet, the stepped wedge design still allows a sound scientific evaluation in a RCT design and address important ethical considerations, thereby increasing the possibility of a high number of participants and compliance, leading to stronger estimates in our data analysis.

Some limitations of the intervention design also deserve to be mentioned. As all employees will receive the intervention, it is not possible to blind participants or those involved in delivering the intervention. Hence, information bias may appear, particularly when outcomes are subjective. E.g. it is possible that participants are likely to report more positive health outcomes due to extended awareness of changes in these conditions after having received the intervention, leading to stronger effect-estimates of the intervention [28].

Furthermore, selection bias may challenge the generalizability of the results: it is plausible that healthy workers are more likely to stay at work longer than those who are injured or made sick from work [29] (healthy worker selection bias). This may reduce the potential to identify adverse health effects from work, leading to weaker estimates of the effect of risk factors on the health outcomes. However, by using a screening questionnaire we can examine if those who want to participate are different from those who do not want to participate.

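### Read literally, the missing-data sentence deletes every worker with any missed round, which contradicts the stated intention-to-treat principle and discards data the mixed model can use

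*Protocol article*

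**What the plan says.** Two statements in the protocol article's section 'Effect evaluation and analyses' meet on this point. The first sets the principle and the model: "The quantitative data will be analyzed based on the intention-to-treat principle in linear mixed models with random slope and intercept". Four sentences later comes the missing-data rule: "Participants missing data on exposure or outcome variables will be excluded from analyses". Between them, the exposure is defined: "The intervention will be included as a categorical variable with two levels, comparing the intervention period with the control period as a fixed effect".

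The section on data collection places health checks at baseline and about every third month, "summing up to five data collections in total". The analysis section lists four outcome domains: musculoskeletal disorders, psychosocial wellbeing, safety culture and workability.

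Under 'Strengths and limitations' the authors remark that "it is plausible that healthy workers are more likely to stay at work longer than those who are injured or made sick from work". The article states no expected missingness or dropout rate.

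**The concern.** The exclusion rule names participants, not measurements or visits. In a study with one follow-up the difference would be small. With five rounds it is large, because the chance of a complete record shrinks with every round. A worker seen at four of five health checks would contribute nothing.

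This conflicts with intention-to-treat, which keeps enrolled workers in the analysis. It also gives up a main advantage of the chosen model: a likelihood-based mixed model uses incomplete records and is valid when missingness depends on observed data. Precision is certain to be lost under the literal rule. The population analysed also shifts to workers who attended throughout, which can move the estimate under further conditions.

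Because the sentence can be read in more than one way, the analysis set could also be settled after the data are seen.

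**Working it through.** **The plan's own figure.** The only sample-size figure is a cluster size of 65. It cannot be reproduced, because no effect size is given; the inputs shown are "an expected variance of 2.1, an Alpha value of 0.05, and a power of 80"%. With variance 2.1, two-sided alpha and 65 per arm, the implied difference is √2.1 × (1.960 + 0.842) × √(2/65) = 0.71. This is a separate matter and does not affect what follows.

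**Inputs.** From the document: five rounds, exclusion of participants, and 65 per cluster. Assumed, because the document gives no values: 5%, 10% or 20% missing, four start groups of 65, and within-person correlation 0.6.

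**Step 1: participants excluded under the literal rule.**

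- Independent missingness m per round: share excluded = 1 − (1 − m)^5. This gives 1 − 0.95^5 = 0.226, 1 − 0.90^5 = 0.410 and 1 − 0.80^5 = 0.672. Of 65 workers, about 50, 38 or 21 remain.
- Permanent dropout h per interval (four intervals, all seen at baseline): share excluded = 1 − (1 − h)^4. This gives 0.185, 0.344 and 0.590.

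**Step 2: collected measurements discarded.** Under dropout the share is 1 − 5(1 − h)^4 / Σ(1 − h)^i, with i from 0 to 4. At 5% it is 1 − 4.073/4.524 = 10%. At 10% it is 1 − 3.281/4.095 = 20%. At 20% it is 1 − 2.048/3.362 = 39%.

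**Step 3: loss of precision.** The variance of the intervention effect is the matching diagonal element of (Σ X′V⁻¹X)⁻¹. X holds the five period effects and the intervention indicator, and V is built from the assumed correlations (random intercepts only, no random slope). Let f be the standard error with complete cases divided by the standard error of the same model on all available data. If the latter has 80% power, complete cases have power Φ(2.802/f − 1.960). For f = 1.55 this is Φ(1.807 − 1.960) = Φ(−0.153) = 44%.

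| Setting | f at 5 / 10 / 20% | Power at 5 / 10 / 20% |
|---|---|---|
| Independent, no worksite component | 1.11 / 1.23 / 1.55 | 71 / 62 / 44% |
| Dropout, no worksite component | 1.05 / 1.10 / 1.24 | 76 / 72 / 62% |
| Independent, worksite ICC 0.05 | 1.04 / 1.10 / 1.27 | 77 / 72 / 60% |
| Dropout, worksite ICC 0.05 | 1.02 / 1.04 / 1.12 | 79 / 77 / 71% |

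The factors are approximate; a recheck agreed to within about 0.02. The first entry in the last row is 1.018 before rounding, hence 79%. The rows with ICC 0.05 assume a cluster autocorrelation of 0.8, so part of the worksite variation changes from round to round.

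**Step 4: bias.** In simulations where dropout depended on the score and workers with more pain were assumed to benefit more, the true effect was −0.50. With 27% lost, complete cases gave −0.43 and all available data −0.47. With a constant effect and 24% lost, complete cases gave −0.49 and all available data −0.51 (Monte Carlo standard error 0.007), so there was no material bias.

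**The case against.** The strongest reply is that the sentence may not mean what it literally says. It closes a description of a repeated-measures mixed model to be run in SAS or SPSS, whose mixed procedures keep all available rows of long-format data by default. The authors may have meant that missing records drop out, or that only workers with no outcome at all are excluded. The loss would then be far smaller. This stands as a reason to treat the literal reading as conditional. It does not rescue the wording, which says neither of these things.

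A second reply is that missing-data detail commonly sits in the analysis plan, which is not shown. That is why the absence of an imputation or sensitivity plan is not raised here. The article, however, states a rule, and that rule conflicts with the principle in the same paragraph.

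Three stronger readings are tempting, and the document does not support them:

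- *That the loss will be selective.* The remark about healthy workers is worded as plausible and concerns generalisability and estimates for risk factors. It does not describe dropout between health checks.
- *That excluding on exposure means selecting on participation.* Exposure is defined by period, not attendance, so it should rarely be missing. The phrase may simply be generic.
- *That the estimate will be biased.* Step 4 shows material bias only when the effect is assumed to vary with health, and there the available-data analysis removes only part of it.

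The largest losses also should not be read as expected. They come from independent intermittent missingness with no worksite component. Dropout, which an argument about leavers implies, costs less.

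**Conclusion.** The sentence is wrong as written. Taken literally, it replaces the promised intention-to-treat analysis with a complete-case analysis and throws away measurements that the chosen model can use. Taken loosely, it does not define who is analysed.

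The size depends on missingness that the document does not state. At assumed rates of 5% to 20%, between 19% and 67% of participants would be excluded, and a power of 80% would fall to somewhere between about 79% and 44%. The upper end assumes 5% dropout per interval with a worksite component; the lower end assumes 20% independent missingness without one. All power figures rest on four start groups of 65 and a within-person correlation of 0.6, neither of which is a design fact in the document.

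The contradiction and the direction of the precision loss under the literal rule are secure. The amount is not. Bias is a possibility that needs both health-related loss and an effect that differs with health.

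**What to change.** Replace the exclusion sentence with wording such as: *All participants with at least one outcome measurement are included; all available measurements enter the likelihood-based mixed model, assuming data are missing at random; intervention status is assigned by the worksite's scheduled period, irrespective of participation.* Keep the complete-case analysis only as a sensitivity analysis.

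If the authors meant only that missing records drop out, the same wording makes that explicit.

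The cost is one sentence. No extra data are needed, and the SAS and SPSS mixed procedures already work this way with data in long format. The change should be made before the effect analysis. It does not protect against missingness that depends on unobserved values.
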